	**Usability**					
		User friendliness and usability	System Usability Scale (SUS) [61]		✓	
		Patient trust to health service	Patient Trust Assessment Tool (PATAT) [62]		✓	
		Quality of mobile health apps	User Version of the Mobile Application Rating Scale (uMARS) [63]			✓
	**Feasibility**					
		Recruitment rate	Percentage of patients included in the study out of the eligible patients	✓	✓	✓
		Patient compliance	Percentage of patients completing the questionnaires	✓	✓	✓
		Patient retention	Percentage of patients adhering to the app	✓	✓	✓

^a^CAPABLE: Cancer Patients Better Life Experience.

^b^PROM: patient-reported outcome measure.

^c^EORTC: European Organization for Research and Treatment of Cancer.

^d^QLQ-C30: Quality of Life Questionnaire-Core 30.

^e^HRQoL: health-related quality of life.

^f^Of the FACT-M, we use the Melanoma Subscale and the Melanoma Surgery Subscale, items specific to quality of life in patients with melanoma. High scores show a high quality of life. Testing has shown that the FACT-M is a reliable and valid instrument to assess quality of life in patients with melanoma.

^g^The EQ-5D is a standardized 5-level, 5-dimensional multi-attribute utility questionnaire that measures mobility, self-care, usual activities, pain/discomfort and anxiety/depression, using a five dimension scale.

^h^Psychological distress will be assessed with the Hospital Anxiety and Depression Scale (HADS). The HADS, a 14-item questionnaire, assesses symptoms of mood disturbance, yielding separate scale scores for anxiety and depression, as well as a total score.

^i^Immunotherapy-specific questionnaire. In assessing quality of life in patients with cancer, it is recommended to use a generic and cancer-specific measure of quality of life plus a treatment-specific questionnaire. However, to date the available validated measurements do not include the problems and symptoms of immunotherapy. Therefore, we identified, based on literature and expert opinion, 19 symptoms and created a symptom list based on items of the EORTC item Library.

^j^Fulfilment of information needs will be measured by the EORTC QLQ-INFO25 questionnaire. This validated 25-item questionnaire incorporates four information provision subscales: perceived receipt of information about the disease, medical tests, treatment and other care services.

^k^QLQ-INFO25: Quality of Life Questionnaire-Information 25.

### Sample Size Calculation

As this is an exploratory study, a rough sample size calculation was performed based on preliminary changes in fatigue in the control cohort and feasibility parameters. In the control cohort (currently composed of 70 patients with melanoma that started with ICIs), an increase of 15 points in fatigue is shown in the first 3 months of treatment (nonpublished data). When providing the CAPABLE system to patients in the pilot study, we expect significantly less worsening of patients’ fatigue levels (by 5 points less increase in fatigue). With a 10-point difference and an SD of 20, the selected effect size is 0.5. Since the inclusion period is restricted to 6 months due to project obligations, we use an enrollment ratio of 0.3 (two-third of the control cohort and one-third of the CAPABLE cohort). Together with a 2-sided α of .05 and an accepted power of 70%, the needed sample size would be 139 patients, of whom 107 will be enrolled in the control cohort and 32 will be enrolled in the CAPABLE pilot study. We anticipate a dropout rate of 5%-10% because of unforeseen rapidly progressive diseases that might occur in this patient population. Questionnaire dropouts are considered minimal because the research team will see the patient around their 3- and 6-month follow-up at the patient’s hospital appointments. A compliance rate of 60% to participate in and use the CAPABLE system is considered feasible and clinically acceptable, meaning 36 patients have to be included to meet this feasibility end point. Therefore, we need to have 60 eligible patients in the 6-month inclusion period.

### Statistical Methods

Descriptive statistics will be calculated to provide information about the patient population. The mean scores of fatigue and other questionnaire outcomes will be calculated using algorithms in the existing literature, and these scores will be used as end points for analyses. Summarizing and visualizing methods such as line graphs will be used to make the data more interpretable. Effect sizes will be calculated using standard statistical procedures. The difference in fatigue (improvement or worsening) over time (baseline and follow-up moments) will be analyzed either using a linear mixed model or generalized estimating equation analysis. We will adjust for baseline patient-reported outcome scores and other covariates such as sociodemographic variables, disease, and treatment characteristics. To compare the mean fatigue scores between the group receiving the CAPABLE intervention and the control group at each individual time point, we will use *t* tests or Mann-Whitney U tests. Patients will be individually matched on sex, age, tumor staging (stage III or IV), and treatment (mono- or combination therapy). For differences in fatigue between the groups over time, we will use repeated measures ANOVA. A *P* value of <.05 will be seen as statistically significant; however, according to Cocks et al [65], a mean difference in change scores (per subdomain) can be seen as clinically relevant even if this is not statistically significant. Therefore, statistical and clinically meaningful differences will be analyzed. However, as this is an exploratory study, analysis will mostly consist of descriptive statistics, as *P* values are expected to render most outcomes nonsignificant.

Missing items from the questionnaires will be imputed according to the corresponding guidelines. The scale scores of the EORTC QLQ-C30 will be set to missing if fewer than half of the items on a given scale are answered. Where at least 50% of the relevant scale scores will be present, the missing values can be replaced by the mean of the present values. Statistical analyses will be done using R (R Core Team) [66].

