### Study End Points

#### Primary Outcome

The primary end point of this study is the change in fatigue between baseline and 3 and 6 months, as measured by The European Organization for Research and Treatment of Cancer (EORTC) Quality of Life Questionnaire-Core 30 (QLQ-C30) [56]. The changes in fatigue over time in the intervention cohort will be compared to the changes in fatigue over time in the control cohort. Fatigue is constructed out of 3 questions: “Did you need to rest?” “Have you felt weak?” “Were you tired?” Responses range from 1 (not at all) to 4 (very much) and are linearly transformed into a fatigue scale ranging from 0 to 100, with higher scores representing more experienced fatigue.

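### Baseline fatigue is both an analysed time point and a covariate, and the primary between-group contrast is assigned to a repeated-measures ANOVA with no covariates and no stated primary model

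*Protocol article*

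**What the plan says.** The Primary Outcome section defines the comparison: "The changes in fatigue over time in the intervention cohort will be compared to the changes in fatigue over time in the control cohort". The contrast of interest is therefore the between-cohort difference in change in QLQ-C30 fatigue.

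Statistical Methods then gives three routes to it:

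- A longitudinal model, in which fatigue "over time (baseline and follow-up moments) will be analyzed either using a linear mixed model or generalized estimating equation analysis". The next sentence is "We will adjust for baseline patient-reported outcome scores and other covariates such as sociodemographic variables, disease, and treatment characteristics".
- Tests of raw means at each visit (t or Mann-Whitney), with no covariates named.
- "For differences in fatigue between the groups over time, we will use repeated measures ANOVA", again with no covariates named.

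The section also plans a design-stage control: "Patients will be individually matched on sex, age, tumor staging (stage III or IV), and treatment (mono- or combination therapy". Baseline fatigue is not among the matching variables, and the article does not say which of the three routes uses the matched set.

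On missing data, the text deals with items within a scale ("Missing items from the questionnaires will be imputed according to the corresponding guidelines"). The Sample Size Calculation expects 5%-10% dropout "because of unforeseen rapidly progressive diseases that might occur in this patient population" and little questionnaire dropout beyond that.

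**The concern.** The control cohort is historical. The Discussion adds that it was collected during the COVID-19 pandemic, which may have worsened its quality-of-life scores, so a difference in baseline fatigue between the cohorts is plausible. Matching and covariate adjustment are the only protections named.

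The text weakens the second protection in two ways. Baseline is listed among the analysed moments and again as a covariate, and in the most ordinary form of such a model the adjustment cannot reach the change contrast. In addition, the sentence that addresses the difference between groups over time names a method without covariates. Followed as written, it yields an essentially unadjusted, complete-case contrast, although a better method is already named a few lines above.

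**Working it through.** **The plan's own figure.** Inputs from the Sample Size Calculation: difference 10, SD 20, two-sided alpha 0.05, power 70%, ratio 0.3.

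- Control n = (1 + 1/0.3) × (1.960 + 0.524)² × (20/10)² = 107. CAPABLE n = 0.3 × 107 = 32.1. The stated 107 + 32 = 139 reproduces (140 if 32.1 is rounded up).
- Power at 107 v 32 is 69.9% by the normal approximation and 69.3% by the noncentral t.

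**Why main-effect adjustment does not reach the contrast.** Let the model contain group, visit, group-by-visit and a covariate X with one coefficient c at every visit. With complete data, the fitted group difference at visit j is (raw difference at j) − c × (group difference in mean X). Subtracting the baseline difference from the 3-month difference cancels the c term. What remains is the raw difference in change, whatever c is, and this also holds when X is baseline fatigue itself.

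**Numerical check of that algebra.** 60 simulated data sets, 107 v 32, three visits, SD 20. Assumptions, not from the documents: no true effect, within-patient correlation 0.5, and an unmatched confounder present in 60% v 30% that adds 10 points to the change. The expected bias is (0.30 − 0.60) × 10 = −3.0.

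| Specification | Mean 3-month estimate |
|---|---|
| Baseline in response, unadjusted | −2.95 |
| Baseline in response, covariates as main effects | −2.95 (largest difference from unadjusted about 7e-13) |
| Baseline in response, covariates interacting with visit | −0.13 |
| Follow-up scores only, baseline and confounder as covariates | −0.08 |

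With 10% of follow-up visits missing at random, the first three rows become −2.84, −2.73 and −0.02. The table shows which specifications adjust. It does not estimate the bias in this trial.

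**What matching leaves open: baseline fatigue.** Assume equal SDs, correlation r, no intervention effect given baseline, and a 5-point baseline difference.

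- The raw change contrast shifts by −(1 − r) × 5: −2.5 at r = 0.5 (−3.5 at r = 0.3, −1.5 at r = 0.7).
- The raw 3-month comparison shifts by r × 5: +2.5 at r = 0.5 (+1.5 at r = 0.3, +3.5 at r = 0.7).

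Two of the listed analyses would thus err in opposite directions on the same data.

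**Complete cases.** Classical repeated-measures ANOVA uses patients with all three visits. With equal loss in both cohorts (noncentral t, effect size 0.5):

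| Cohorts | No loss | 5% loss | 10% loss |
|---|---|---|---|
| 107 v 32 | 69.3% | 66.6% | 64.8% |
| 107 v 36 | 73.2% | 70.8% | 68.1% |

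These are upper bounds on what the ANOVA itself costs, because a patient with no follow-up score is lost to a follow-up-only model too.

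**Precision.** The variance of a baseline-adjusted contrast relative to a change score is (1 + r)/2, or 0.75 at r = 0.5. If 20 is the SD of change, power at 107 v 32 rises from 70% to about 82% (about 87% at r = 0.3 and 77% at r = 0.7), before any cost of covariate imbalance.

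**The case against.** The strongest reply is that the plan states in plain words that it will adjust, and that whether covariates interact with visit is detail for an SAP that is not shown. The mention of baseline and follow-up moments may only describe the interval over which change is measured. This stands in part: main-effects-only entry is an inference, and two specifications that the text permits remove nearly all of the simulated confounding. A reader might infer that the primary model does not adjust at all; the documents do not support that.

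A second reply is the matching. It covers mono/combination therapy and stage, so a bias built on a different therapy mix in the two cohorts describes something the plan says it will prevent. That stands, and no such figure is claimed here. Matching does not cover baseline fatigue.

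Third, nothing in the article says that patients with a missed visit are deleted. That is a property of classical repeated-measures ANOVA, not a stated rule, and the expected loss is small. The ANOVA is also listed in addition to the mixed model or GEE, not instead of them.

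Finally, the study is an exploratory pilot whose analysis is expected to be mostly descriptive. This limits the weight of the point but does not settle which estimate will be read as the result.

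**Conclusion.** The point holds in a limited form. The article does more than leave detail open. It gives baseline two roles, and it names a covariate-free method for the contrast that defines the primary endpoint, beside two other routes and with no order among them.

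The loss of adjustment is exact with complete data, and nearly so with 10% of visits missing, but only if baseline is in the response and covariates are main effects. The 2.5-point shift is an illustration that rests on an assumed 5-point imbalance and r = 0.5 (1.5 to 3.5 points for r from 0.7 to 0.3), a quarter of the 10-point planning difference. The complete-case cost is at most about 3 to 5 percentage points of power, with possible selection because dropout is attributed to progression.

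A reader might go further and conclude that GEE must be removed or that only a follow-up-only model is valid. Neither follows: GEE can carry the same terms, and a model with baseline in the response and covariate-by-visit terms also removed the simulated bias.

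**What to change.** Name one primary between-group analysis: the linear mixed model already listed, or GEE with the same terms.

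- Response: the 3- and 6-month fatigue scores.
- Covariates: baseline fatigue, sex, age, stage and mono/combination therapy, each interacting with visit.
- Estimate: group-by-visit, giving the 3-month group difference, with the 6-month difference from the same model.
- If baseline is kept in the response instead, do not also enter it as a covariate, and let the confounders interact with visit.
- Drop repeated-measures ANOVA for this contrast, and label the raw visit-wise tests descriptive.
- Keep a change-score analysis as a sensitivity analysis. In non-randomised cohorts it and the baseline-adjusted analysis can estimate different things.

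The cost is wording and a few degrees of freedom for the interactions. Patients with no follow-up score remain outside the follow-up-only model and should be counted and described by cohort.

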### Patient and Public Involvement

One of the CAPABLE consortium members is an Italian patient association that was involved in the development of the CAPABLE app. Furthermore, the development of CAPABLE went through multiple research phases. Patient and clinician interviews were held to establish baseline needs and wish for the CAPABLE system (P20CAP; IRBd20-085), of which a paper is published [43]. HCPs provided valuable input for the clinical validation of the implemented guidelines. Furthermore, multiple patients and HCPs provided their valuable input to enhance the quality of the system during the development of the CAPABLE app through multiple usability testing rounds (P21CAP; IRBd21-139). The results of the study will be communicated to participants if wish.

### Ethics Approval

Ethical approval was granted by the Medical Ethical Committee of NedMec (Amsterdam, The Netherlands) under reference number 22-981/NL81970.000.22. Any amendments will be reviewed by this Medical Ethical Committee. CAPABLE is registered as a medical device trial according to the Medical Device Regulation, article 62. The trial is prospectively registered at ClinicalTrials.gov (NCT05827289). Original informed consent signed by patients allows for the analysis of the primary and secondary outcomes of this study. In case additional data needs to be analyzed, additional informed consent will be asked. Subject data will be pseudonymized and key-coded. No compensation is provided to participating patients. This study is conducted in accordance with the principles of the Declaration of Helsinki, version 9, October 2013, and the Medical Research Involving Human Subjects Act (WMO), including International Organization for Standardization (ISO) 14155 (medical device use).

## Results

Inclusion in this trial started late in April 2023 and is currently enrolling. We expect to finalize inclusion by the end of August 2023. The expected last follow-up measurement will be collected in February 2024, after which data cleaning and data analysis will start. Preliminary data analysis will be carried out in December 2023 due to a project deliverable deadline by the end of December 2023.

## Discussion

In this pilot study, we will explore the effect of using the CAPABLE app immediately after melanoma diagnosis in 36 patients, providing symptom monitoring, education, and well-being interventions during their first phase of treatment with ICIs, on 3- and 6-month HRQoL outcomes such as fatigue and functioning, and the patient acceptability of using a system such as CAPABLE. Since treatment with ICIs is becoming standard therapy for patients with high-risk and advanced melanoma, more and more patients experience treatment-related AEs. One of the most common symptoms of this treatment is fatigue. Consequently, a decrease in short- and long-term HRQoL can occur in these patients. An approach to improving symptom control and HRQoL outcomes is to use an eHealth tool. eHealth apps may contribute to improving HRQoL by addressing the unmet supportive care and information needs of these patients by enabling autonomy and self-management. Moreover, eHealth tools have shown promising results in improving fatigue by stimulating physical exercise, psychoeducation, mindfulness-based interventions, and yoga. However, previous studies focused on eHealth apps providing either symptom monitoring or interventions targeting fatigue.

It is hypothesized that the CAPABLE intervention will limit the increase in fatigue in patients with melanoma receiving ICIs by 10 points at 3 months after the start of treatment compared to a similar patient group receiving standard care. Furthermore, it is hypothesized that the system will be feasible to implement during ICI treatment in clinical practice. This system will be evaluated by 36 patients for 3-6 months from the start of their ICI treatment. End points of the study will be measured at baseline, 3 months, and 6 months after the start of treatment.

Several limitations of this pilot study should be noted. First, the intervention period will be 3 to maximally 6 months due to the limited number of well-being interventions in the mobile app and information provision focusing on the first period of treatment. Therefore, we will not be able to evaluate the long-term effects of the CAPABLE mobile intervention. Second, the inclusion period will be restricted to 6 months, as the time frame of the study is limited by project restrictions and available funding. Third, the control group is collected before the intervention group (ie, the CAPABLE cohort). Because of time restrictions in the project and the limited number of patients available in the hospital, it was necessary to create 2 separate prospective cohorts instead of using a randomized design. Moreover, the control group was collected during the COVID-19 pandemic, and this might have negatively influenced the HRQoL outcomes. Furthermore, we chose the short EORTC QLQC30 fatigue scale to measure our primary outcome, as we already use this questionnaire in our daily clinical routine, facilitating future implementation. As it is short, it minimizes patient burden. Furthermore, it was previously shown that there was no difference in chronic fatigue as measured by the EORTC QLQ-C30 and the validated Fatigue Assessment Scale (FAS) in Hodgkin lymphoma survivors [67]. Lastly, this pilot study does not include the possible relevance of supportive care provided for patient’s informal caregivers. It is well-known that informal caregivers or relatives of patients with cancer experience high caregiver burden and distress [68]. eHealth interventions could offer a convenient approach for providing support to the informal caregivers of individuals facing cancer [69]. Future studies with the CAPABLE app should focus on including support for informal caregivers.

Nevertheless, this pilot trial has several strengths, including the prospective study design of the CAPABLE group and the control group. Furthermore, both study groups are collected from a population receiving standard care and do not participate in experimental trials. The CAPABLE smartphone app is developed following user-centered design principles and in close collaboration with patients, app developers, component developers, and technical and clinical staff. Initial prototypes were built after content-generating interviews with patients and HCPs, following 3 rounds of user experience and user interface testing in both target populations. Consequently, the content offered in the CAPABLE app is of high quality and reviewed by the local medical staff in collaboration with patients. Last, although not primarily focusing on evaluating the change in care structures, it is worth mentioning that an eHealth tool such as CAPABLE may lead to earlier intervention for immune-related AEs and psychological complaints. A future and larger trial should focus on the impact of the implementation of such tools and their effect on existing care structures.

In conclusion, the CAPABLE pilot study will provide preliminary evidence about the effect, usability, and feasibility of the CAPABLE system, which may encourage further studies with this eHealth app. A similar pilot trial with the same CAPABLE system but for another population is currently enrolling patients in an Italian hospital. These studies will be the first to provide a system containing symptom monitoring, information provision, and well-being interventions in one eHealth tool. When positive results are generated on the primary outcome, outcomes should be validated in a larger randomized controlled trial, keeping end points for possible implementation in mind. Adding the CAPABLE system to active treatment is hypothesized to decrease fatigue in patients with high risk and advanced melanoma during treatment with ICIs compared to a control group receiving standard care.

## Abbreviations

AE: adverse event
CAPABLE: Cancer Patients Better Life Experience
CRF: cancer-related fatigue
CTCAE: Common Terminology Criteria for Adverse Events
EHR: electronic health record
EORTC: The European Organization for Research and Treatment of Cancer
FAS: Fatigue Assessment Scale
GAD-7: Generalized Anxiety Disorder-7
HCP: health care professional
HRQoL: health-related quality of life
ICI: immune checkpoint inhibitor
ISO: International Organization for Standardization
NCI: National Cancer Institute
NKI: Netherlands Cancer Institute
PHQ-9: Patient Health Questionnaire-9
PRO-CTCAE: Patient-Reported Outcome version of the Common Terminology Criteria for Adverse Events
QLQ-C30: Quality of Life Questionnaire-Core 30
SUS: System Usability Scale
VC: Virtual Capsule
WMO: Medical Research Involving Human Subjects Act
